## Abstract

Background: The classic mid-trimester preterm premature rupture of membranes (PPROM) is defined as a rupture of the fetal membranes prior to 28 weeks of gestation (WG) with oligo/anhydramnion; it complicates approximately 0.4–0.7% of all pregnancies and is associated with very high neonatal mortality and morbidity. Antibiotics have limited success to prevent bacterial growth, chorioamnionitis and fetal inflammation. The repetitive amnioinfusion does not work because fluid is lost immediately after the intervention. The continuous amnioinfusion through the transabdominal port system or catheter in patients with classic PPROM shows promise by flushing out the bacteria and inflammatory components from the amniotic cavity, replacing amniotic fluid and thus prolonging the PPROM-to-delivery interval. Objective: This multicenter trial aims to test the effect of continuous amnioinfusion on the neonatal survival without the typical major morbidities, such as severe bronchopulmonary dysplasia, intraventricular hemorrhage, cystic periventricular leukomalacia and necrotizing enterocolitis one year after the delivery. Study Design: We plan to conduct a randomized multicenter trial with a two-arm parallel design. Randomization will be between 22/0 and 26/0 SSW. The control group: PPROM patients between 20/0 and 26/0 WG who will be treated with antibiotics and corticosteroids (from 22/0 SSW) in accordance with the guidelines of German Society of Obstetrics and Gynecology (standard PPROM therapy). In the interventional group, the standard PPROM therapy will be complemented with the Amnion Flush Method, with the amnioinfusion of Amnion Flush Solution through the intra-amnial catheter (up to 100 mL/h, 2400 mL/day). Subjects: The study will include 68 patients with classic PPROM between 20/0 and 26/0 WG. TRIAL-registration: ClinicalTrials.gov ID: NCT04696003. German Clinical Trials Register: DRKS00024503, January 2021.

## 1. Introduction

Mid-trimester PPROM complicates approximately 0.4–0.7% of all pregnancies and is associated with very high neonatal mortality and severe morbidity [1,2,3,4]. The causes of the mid-trimester PPROM are multifactorial [4]. The mechanism of PPROM is discussed as altered membrane morphology, including marked swelling and disruption of the collagen network, which can be triggered by bacterial products and pro-inflammatory cytokines and involves the activation of matrix metalloproteinases [4,5,6,7].

The propagation of bacteria is an important contributing factor in adverse neonatal and maternal outcomes after PPROM [1,4,8]. Gomez et al. reported that antibiotics failed to eliminate the amniotic infection in 83% of PPROM cases [9]. The “classic PPROM” with oligo/anhydramnion is associated with a short latency period and worse neonatal outcome compared to similar gestational aged neonates [4].

In Germany, the number of pregnant women with mid-trimester classic PPROM has been calculated to be about 5 thousand–7 thousand per year. Generally, about 40% of very preterm infants who survive the initial NICU die during next 5 years of life, and the long-term morbidity of the survivors remain high. Furthermore, more than 40% of surviving neonates following PPROM prior to 25 weeks of gestation develop bronchopulmonary dysplasia (BPD) later on [4,10].

The **fetal inflammatory response syndrome (FIRS)**, a systemic inflammation determined by elevated fetal plasma IL-6 concentrations and histological signs of funisitis in the umbilical cord, is an additional independent risk factor for the occurrence of severe neonatal morbidity [11].

The lavage effect of continuous amnioinfusion could protect the fetus and amniotic cavity from bacterial colonization; reduce the inflammatory response; and thus protect the neonate from major complications, such as pulmonary hypoplasia, sepsis, cerebral palsy and joint deformities [4,12,13,14,15].

Serial amnioinfusions with standard electrolyte solutions have seen little or no effects onto neonatal outcome probably because of the immediate loss of fluid after the intervention and possible negative effect of longtime saline solution on the fetus [4,14,16,17,18,19].

[name] et al. performed the prolongation of the PPROM-to-delivery interval to 49 days in average patients with classic PPROM by using the intensive lavage of the amniotic cavity with Amnion Flush Solution (pump rate 100 mL/h) through a transabdominal catheter with an additionally designed anker system [4,12,20,21].

However, in recently published retrospective results from Japan, the authors did not improve the neonatal outcome by using a low rate of continuous amnioinfusion with Ringer’s lactate solution (40 mL/h) [14,15]. In the current German medical guidelines for the prevention of preterm birth, the amnioinfusion for the treatment of the PPROM is mentioned, but prospective randomized studies must be performed to clarify the positive effect of the continuous amnioinfusion on fetal survival [22].

## 2. Objectives

Principal research question: Does the intervention (continuous amnioinfusion—“flush out” method) reduce the adverse neonatal outcome of patients with PPROM with oligo/anhydramnion and prolong the pregnancy?

Primary hypothesis: The Amnion Flush Method will improve the neonatal outcome after PPROM between 20/0 and 26/0 weeks of gestation.

## 3. Materials and Methods

The full infrastructure of Coordination Center for Clinical Trials (KKS) of Martin-Luther-University Halle Wittenberg will be involved in ICH–GCP (Internation5al Conference on Harmonisation of Technical Requirements for Registration of Pharmaceuticals for Human Use–Good Clinical Practice) compliant data management and handling, randomization, safety management and monitoring of the study.

## 4. Study Setting

The study will be performed in 9 tertiary German perinatal centers, including five leading German universities (Figure 1).

ClinicalTrials.gov: NTC04696003. Filled circles: approved by local ethic committee.

Trial design:

Randomized multicenter trial; two-arm parallel.

Trial registration:

The trial was registered with ClinicalTrials.gov ID: NCT04696003 and German Clinical Trials Register: DRKS00024503.

Protocol version: Nr: KKSH163, 15 December 2020.

The TRIAL has obtained a permission of the Ethical Committee of the Halle University Medical Center (2020-185, 25 January 2021).

Funding:

The study is being funded by the German Federal Ministry of Education and Research (BMBF, No. 01KG2007).

**Eligibility criteria**

**Inclusion criteria:** single pregnancy (from 22/0 to 26/0 weeks of gestation), with classic PPROM with oligo/anhydramnion between 20/0 and 26/0 weeks of gestation. From the beginning of 22/0 weeks of gestation, the PPROM duration must be lower as of five days till randomization. The patients will receive RDS prophylaxis (respiratory distress syndrome) before randomization. The vertical deepest amniotic fluid depot must be <2 cm, and the amniotic fluid Index < 3. The PPROM will be confirmed by positive testing of the placental alpha microglobulin-1 and the amniotic fluid that is clearly lost (Figure 2, flow diagram).

**Exclusion criteria:**

The patients with fetal death, high rupture of membranes, pre-PPROM, premature labor, placental abnormalities, placental abruption, evidence of major structural or chromosomal abnormalities, indication for termination of pregnancy (e.g., HELLP syndrome, pathological CTG (if present), fetal bradycardia, eclampsia and umbilical cord prolapse), cervical insufficiency, placenta previa, signs of chorioamnionitis (maternal fever > 37.8 °C and two or more of the following criteria: uterine tenderness, malodorous vaginal discharge, maternal leukocytosis > 15,000 cells/mm^3^ (without corticosteroids), maternal tachycardia > 100 beats/min and fetal heart rate > 160 bpm) and CRP > 20 mg/dL (C reactive protein).

**Who will take informed consent?**

The authorized physicians of perinatal centers taking part in the trial will identify the potential trial participants with classic PPROM. Eligible women with classic mid-trimester PPROM will be asked for their written informed consent at the time of admission to the hospital, after having received oral and written information. Patients, who are not able to understand the informed consent will not be included. Additionally, for five years, all patients undergoing a fetal surgery therapy in hospital had filed a motion for a compassionate use from the ethical review committee. Recruitment for “flush out” method via a port-system is ethically sound for PPROM patients with oligo/anhydramnion, based on the available research evidence.

In case of complications, all equipment for emergency interventions will be easily accessible in the perinatal centers. An additional “safety net” for the finalization of the study and induction of delivery was established to avoid any complications.

**Intervention and control groups**

**Control group**

The PPROM patients of the control group receive the standard therapy related to the German Guidelines, including antibiotic therapy (Amoxicillin/Clarithromycin therapy or 7 days Amoxicillin and once Azithromycin 1 g per oz) or other antibiotics according to recommendations of the physicians from the microbiology department based on the culture results for at least 7 days [22]. There must be a daily blood analysis (hemoglobin, leucocytes, thrombocytes, CRP and interleucine-6) and a cervical smear every 5 days. The RDS prophylaxis must be performed before randomization.

**Amnion Flush interventional group** (Figure 3)

The PPROM patients of the Amnion Flush group will receive the standard therapy related to the German Guidelines, like the control group [22]. Additionally, after the amnioinfusion of 300 mL (Amnion Flush Solution Serumwerk AG, Bernburg, Germany) through the 22G needle (Figure 4A), under local anesthesia, an ultrasound-guided perinatal catheter with an anchor system (0.65 mm Diameter, CE 0481, PakuMed GmbH, Essen, Germany) will be inserted into the amniotic cavity through the 18G needle for the continuous amnioinfusion with 100 mL/h of Amnion Flush Solution, (Serumwerk Bernburg AG, Germany) until delivery (latest on beginning of 34/0 weeks of gestation) [4,12,13] (Figure 4B,C).

**Detailed description of the perinatal catheter implantation**

The catheter implantation will be performed in the operation room in aseptic conditions. Before the catheter implantation, the amnioinfusion with about 300 mL of Amnion Flush Solution will be performed by using a 22-gauge needle, under ultrasound control (Figure 4A).

The gynecologist must have experience with at least 100 amniocenteses because of the difficult conditions for the puncture related to anhydramnion.

The operation table allow for patients to be kept in the maximum Trendelenburg position in order to avoid the complete loss of infused Amnion Flush Solution because of PPROM. If patients complain about uterine contractions, the single short of Partusisten 25 µg will be slowly infused i.v.

The appropriate location for the catheter implantation (preferred area is the uterine fundus without placenta) will be identified by using ultrasound. Local anesthesia with Xylocaine 1% 10 mL will be injected [20]. The 18-gauge needle will be inserted into the amniotic cavity (Figure 4B).

The anchor catheter will be inserted through the needle. The 18 G needle will be removed. The catheter will be fixed up by using the sterile transparent foil (Figure 4C).

The Amnion Flush Solution will be infused by using standard medical pumps, at a rate of 100 mL/h (±20 mL). Daily ultrasound control must be performed to validate the intra-amniotic catheter position and the deepest deport of the amniotic fluid. The deepest pool of amniotic fluid should be stabilized (target 4 cm). The catheter should be replaced if indicated (e.g., delivery or catheter dislocation or plugging), but the latest should be every 30 days to avoid contamination and/or inflammation.

**Outcomes:**

**Primary outcome:** survival (binary yes/no) without major morbidities (severe bronchopulmonary dysplasia (BPD), and/or grade 3 or 4 intraventricular hemorrhage (IVH 3–4), and/or necrotizing enterocolitis (NEC) indicated for surgical intervention, and/or cystic periventricular leukomalacia (cPVL)) obtained one year after the delivery [23].

**Secondary outcomes:** Gestational age at delivery, duration of PPROM-to-delivery interval, perinatal mortality, incidence of histological affirmed chorioamnionitis, incidence of FIRS and/or maternal sepsis, cord-artery pH, APGAR scores, neonatal outcome at calculated age 36 weeks of gestation: duration of O_2_-supplementation, retinopathy of prematurity. Participants with surviving babies will send a prepaid validated outcome questionnaire at 12 months after the birth of their baby. The independent University Center of Clinical Studies of Martin-Luther-University Halle-Wittenberg will receive the copies of pediatric examinations performing monitoring and final statistical evaluation. Neurodevelopmental assessments, as well as the check-up, of the surviving children will be performed in tertian medical centers by trained pediatric specialists.

**Participant timeline**

The study site visits for monitoring the clinical trial will be carried out by chief and assistant monitors. During the clinical phase, the chief monitor will visit the medical centers every 6 months (see Table 1), thereby being available to be on staff, supervising the assistant monitors, and in order to address and solve any problems arising.

They will review the progress of recruitment and ensure participants’ rights and safety and the adherence to protocol regulatory compliance. During the query process by the KKS, which implies another month of study-site visits (beyond the end of recruitment), they will verify unclear data and obtain corrections. The chief monitor will also make sure that plenty of CRFs are available as staff, and questionnaires will be given to mothers to fill in prior to discharge from the hospital.

**Sample size and Statistic**

The sample-size calculation was based on the primary outcome (binary yes/no) survival without major morbidities (severe bronchopulmonary dysplasia (BPD), and/or grade 3 or 4 intraventricular hemorrhage (IVH 3–4), and/or necrotizing enterocolitis (NEC) and/or cystic periventricular leukomalacia (cPVL)).

The intervention is expected to prolong the gestation by around two weeks, resulting in an increase of the one-year survival rate without major morbidities after 27 gestational weeks of 67% (hazard = 0.0334). Based on Chen et al. (2016), the one-year survival rate without major morbidities after 25 weeks of gestation is around 36% (hazard = 0.0851) [23]. To be more conservative, the sample-size calculation was based on a hazard = 0.035 for the interventional group. Using a recruiting period of 21 months (four women per month) and an individual follow-up of one year, 34 women are needed in each group for a two-sided log-rank test with 5% significance level, a power of 80% and a loss-to-follow-up rate of 10% per year (hazard = 0.0088). Calculations were performed by PASS software.

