**Trial Status:**

Protocol number KKSH163, Version No. 1.0, 27 October 2020.

Recruitment began: March 2021.

The approximate date when recruitment will be completed: January 2024.

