**Figure 4 life-12-01351-f004:**
[figure not shown]

[figure not shown]
(**A**) Amniocentesis with 22G needle and amnioinfusion 300 mL of Amnion Flush Solution (Serumwerk AG, Bernburg, Germany). (**B**) Amniocentesis with 18G needle under local anesthesia and introduction of the catheter. (**C**) The intra-amnial catheter (arrow) is covered by Tagaderm film. The rate of intra-amnial infusion is 100 mL/h (Amnion Flush Solution, Serumwerk AG, Bernburg, Germany).

**Table 1 life-12-01351-t001:** Time points of visits and procedures every 6 months (x) and per month (xx).

	Screening Day −5–0	Randomization Day 0	Therapy Day 0–85 (max)				Follow-Up Day 01–365 (± 30 d) Postpartum			
			Daily	Every 7 d (±1 d)	As Needed	Dies Natus	1 d Postpartum	Day of Release from Hospital	Calc. GA 36 (0) (±3 d)	365 d Postpartum (±30 d)

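### The stated 80% power with 34 women per group is not delivered: with one year of follow-up, power at the planning hazards is about 65–71%

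*Protocol article*

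**What the plan says.** All inputs stand in the protocol article, under Sample size and Statistic:

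- Control group: "the one-year survival rate without major morbidities after 25 weeks of gestation is around 36% (hazard = 0.0851").
- Intervention group: an expected "one-year survival rate without major morbidities after 27 gestational weeks of 67% (hazard = 0.0334"). The calculation itself uses a hazard of 0.035, described as more conservative.
- Test and error rates: "two-sided log-rank test with 5% significance level, a power of 80% and a loss-to-follow-up rate of 10% per year (hazard = 0.0088").
- Size: "Using a recruiting period of 21 months (four women per month) and an individual follow-up of one year, 34 women are needed in each group".

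The Abstract gives the same total: "The study will include 68 patients with classic PPROM".

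The follow-up is fixed elsewhere. Under Outcomes, the primary outcome is a binary status "obtained one year after the delivery". The last column of the visit schedule in Table 1 is "365 d Postpartum (±30 d"). Trial Status adds: "The approximate date when recruitment will be completed: January 2024", with a start in March 2021.

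**The concern.** The power of a log-rank test depends on the number of events, and the number of events depends on how long each participant is observed. A calculation that takes a recruiting period and a follow-up period usually treats the second as the minimum: the last recruit is observed for 12 months and the first for 21 + 12 = 33. In this trial everyone is observed for one year. If the software was given the first design and the trial runs the second, the size is too small for the power claimed.

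At stake is the justification for the 68 women. The risk of missing the planned effect would be about half as large again as stated, and anyone reading a null result against a nominal 80% would give it too much weight.

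The accrual inputs also disagree. Four women per month for 21 months is 84, while 68 women at that rate take 17 months.

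**Working it through.** **Inputs.** The hazards are per month. Over 12 months they reproduce the stated rates: exp(−12 × 0.0851) = 0.360, exp(−12 × 0.0334) = 0.670 and exp(−12 × 0.0088) = 0.900. The hazard used for the intervention group gives exp(−12 × 0.035) = 0.657. The hazard ratio is 0.035/0.0851 = 0.411, with |ln HR| = 0.8885.

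**Events needed for 80% power, two-sided 5%** (z sum = 1.960 + 0.842 = 2.802):

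- Schoenfeld: 4 × 2.802² / 0.8885² = 39.8.
- Freedman: 2.802² × (1.411/0.589)² = 45.1.

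**Reproducing the plan's 34: common study end at month 33.** With event hazard h, loss hazard c = 0.0088, l = h + c, uniform accrual R = 21 and minimum follow-up F = 12, the event probability is (h/l) × {1 − [exp(−lF) − exp(−l(F+R))]/(lR)}. This gives 0.778 and 0.490, with mean 0.634.

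- Women per group: 39.8/(2 × 0.634) = 31.4 (Schoenfeld) and 45.1/(2 × 0.634) = 35.6 (Freedman). Lachin-Foulkes gives 34.6.
- At 34 per group: 34 × (0.778 + 0.490) = 43.1 events. Power is 78.2% (Freedman), 79.3% (Lachin-Foulkes), 83.1% (Schoenfeld) and about 82% (simulation, 20,000 runs).

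The stated figure therefore fits this design.

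**The design the trial has: everyone censored at 12 months.** The event probability is (h/l) × [1 − exp(−12l)], which gives 0.613 and 0.327, with mean 0.470. At 34 per group, 34 × (0.613 + 0.327) gives about 31.9 expected events.

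| Method | Power at 34 per group | Per group for 80% |
|---|---|---|
| Freedman | 65.4% | 48.02, so 49 |
| Lachin-Foulkes | 66.9% | 46.8, so 47 |
| Simulated log-rank | about 69% | about 44 |
| Schoenfeld | 70.9% | 42.3, so 43 |

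The Schoenfeld power, for example, is Φ(√31.9 × 0.8885/2 − 1.960) = Φ(0.55) = 0.709.

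**The endpoint as a proportion, 36% against 65.7%.** The normal approximation gives 69.6% with all 34 evaluable and 64.8% with 10% lost (30.6 per group). The exact power of the chi-square test is 68.0% with 34. For 80% power, 44 per group are needed, or 44/0.9 = 49 with 10% loss.

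**Difference detectable with 68 women and 80% power.** Against 36%, the intervention rate must be about 70% with 34 evaluable per group (exact chi-square power 80.5%). With about 31 evaluable it must be about 70–71% (at 70%, exact power with 31 is 79.6%; at 71%, the normal approximation with 30.6 gives 79.9%).

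**Accrual.** 4 × 21 = 84, against 68 stated. March 2021 to January 2024 is about 34 months, and 68/34 = 2 women per month.

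**The case against.** Five points can be made for the plan.

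- **The expected rate is 67%; 0.035 is deliberately cautious.** At 0.0334 with 12-month follow-up and loss, log-rank power is 69% (Freedman) to 75% (Schoenfeld), and 71–77% with no loss. Exact chi-square power is 72%. This is better, but still below 80%.
- **Loss may be lower than assumed.** With none at all, the planning hazards give 67–73%.
- **The clock may start at randomization.** Table 1 allows up to 85 therapy days. Adding that maximum for every woman (12 + 85/30.4 = 14.8 months) gives 71–76% with loss. Only all three concessions together pass 80%, and only by one formula: 0.0334, no loss and 14.8 months for everyone give event probabilities of 0.716 and 0.390, hence 37.6 events and 82% (Schoenfeld) or 76% (Freedman). That is not the stated calculation, and Outcomes dates the endpoint from delivery.
- **The software settings are not shown.** The formulas bracket 34 rather than return it exactly, so the common-end design is a plausible reconstruction, not a proven cause. This stands, but the shortfall does not depend on how 34 arose.
- **The January 2024 date is a projection.** It is given under Trial Status in an article written after recruitment began, so slower recruitment than planned is not an error in the calculation. This also stands. The mismatch between 84 and 68 remains, because it lies within one sentence. With fixed one-year follow-up, neither affects the power.

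**Conclusion.** The concern holds. With the one-year follow-up that the document itself specifies, 34 women per group give about 69% log-rank power at the planning hazards, with a range of 65–71% by method, and about 65–70% for a comparison of proportions. The chance of missing the planned effect is about 31%, close to one in three, instead of 20%. No single favourable change of assumption brings it to 80%.

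The figures assume constant hazards in both groups, exponential loss of 10% per year, follow-up counted from delivery and, for the reconstruction of 34 only, uniform accrual. The type I error and the validity of the endpoint are not affected. The wrong figure is the stated power for 68 women.

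**What to change.** Rerun the calculation with every participant censored at 12 months, or as a comparison of two proportions if the binary endpoint is what will be tested. Then correct the paragraph under Sample size and Statistic in one of two ways:

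1. Keep 68 women. Replace the 80% statement with the power they give (about 69% log-rank, or about 65–70% for 36% against 65.7%), and add the difference detectable with 80% power (36% against about 70–71%).
2. Keep 80% power and raise the size to about 43–49 per group, depending on the method and the allowance for loss.

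In the same paragraph, make the accrual inputs agree with 68 women. Report the current recruitment dates as an updated projection, without overwriting the 21 months if that is what the calculation used.

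The first option costs one rerun and one rewritten paragraph, and the stated power becomes less favourable. The second adds 9 to 15 women per group, 18 to 30 in total.

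### The primary outcome is binary at one year, but the sample size rests on a log-rank test with no stated time origin; for the binary endpoint, 34 per arm gives about 70% power, not 80%

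*Protocol article*

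**What the plan says.** Under Outcomes, the primary outcome is "survival (binary yes/no) without major morbidities" (severe BPD, grade 3–4 IVH, NEC with a surgical indication, cystic PVL), "obtained one year after the delivery". The section Sample size and Statistic repeats the classification: "The sample-size calculation was based on the primary outcome (binary yes/no) survival without major morbidities".

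The same section then works in monthly hazards. The control rate is "after 25 weeks of gestation is around 36% (hazard = 0.0851") and the expected intervention rate is "after 27 gestational weeks of 67% (hazard = 0.0334"); a hazard of 0.035 is used for the intervention arm to be conservative. With 21 months of accrual and one year of follow-up per woman, "34 women are needed in each group for a two-sided log-rank test with 5% significance level", with "a power of 80% and a loss-to-follow-up rate of 10% per year (hazard = 0.0088").

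Section 5, Statistical Analysis, says which institute will analyse the data and names no test. The effect is expected to arise because "The intervention is expected to prolong the gestation by around two weeks". Randomisation takes place before birth.

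**The concern.** A yes/no status at a fixed time and a log-rank test answer different questions. The first compares how many infants are alive and free of major morbidity at one year. The second also weighs when each failure occurred, so it needs a start of the clock and a date for every failure. The article gives neither for this test.

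That matters more here than in most trials. Treatment is meant to lengthen the interval between randomisation and birth, which are the two natural time origins. A test that responds to timing can therefore respond to later birth itself, rather than to more children surviving unharmed. The size of the trial is also at stake: if the endpoint is analysed as it is defined, the quoted 80% power belongs to a different calculation.

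**Working it through.** **1. Where the hazards come from.** -ln(0.36)/12 = 0.0851; -ln(0.67)/12 = 0.0334; exp(-0.035 × 12) = 0.657. For loss, -ln(0.90)/12 = 0.0088. So each hazard is a one-year proportion spread evenly over 12 months. The planning hazard ratio is 0.035/0.0851 = 0.411.

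**2. Reproducing 34 per group.** Events needed (two-sided 5%, 80% power):
- Schoenfeld: 4(1.960 + 0.842)²/(ln 0.411)² = 39.8, so 40.
- Freedman: (1.960 + 0.842)² × (1.411/0.589)² = 45.1, so 46.

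| Follow-up assumed | Event probability, control / flush | Schoenfeld, per arm | Lachin–Foulkes, per arm | Freedman, per arm |
|---|---|---|---|---|
| 21 months' accrual, all followed to month 33 | 0.778 / 0.490 | 31.4 | 34.6 | 35.6 |
| 12 months per woman, as the text says | 0.613 / 0.327 | 42.3 | 46.8 | 48.0 |

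The event probabilities in the second row are λ/(λ+η) × [1 - exp(-12(λ+η))] with η = 0.0088. The figure of 34 is reproduced, to within two patients per arm by Lachin–Foulkes and Freedman, only if women are followed for 12 to 33 months and fail at a constant rate throughout. That counts failures after the one-year endpoint. With one year each, 68 women give 68 × (0.613 + 0.327)/2 ≈ 32 events and 65% (Freedman) to 71% (Schoenfeld) power.

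**3. The endpoint as defined: two proportions, 34 per arm.** For 0.360 versus 0.657:
- Difference 0.297; mean proportion 0.509.
- Pooled SE = √(2 × 0.509 × 0.491/34) = 0.121; unpooled SE = √((0.360 × 0.640 + 0.657 × 0.343)/34) = 0.116.
- Power = Φ[(0.297 - 1.960 × 0.121)/0.116] = 69.6%.

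For 0.36 versus 0.67 the same formula gives 73.5%. With 10% loss (34 × 0.9 = 30.6, about 31 evaluable per arm), power is about 65% and 69%. Exact enumeration at 36% versus 65.7% with 34 per arm gives 68% for the uncorrected chi-square test and 60% for Fisher's test. Reaching 80% would need 44 per arm (49 after 10% loss), or 40 (45 after loss) at 36% versus 67%.

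**4. Effect of the clock if the log-rank test is the analysis.** The article gives no event timing, so the following are assumptions: 34 per arm; the same 36% success in both arms; gestational age at randomisation uniform from 22/0 to 26/0; control latency exponential with mean 7 days; flush latency 14 or 49 days longer, capped at 34/0. The article expects about two weeks. Its feasibility series reports a mean PPROM-to-delivery interval of 49 days, so treating all 49 as prolongation is an upper case. Failures occur within 14 days of birth, except for a varied share dated at 36 weeks postmenstrual age. One-sided false-positive rates (nominal 2.5%), for +14 / +49 days:

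| Share dated at 36 weeks | Birth clock, favouring control | Randomisation clock, favouring flush |
|---|---|---|
| 50% | 5.2% / 6.6% | 4.3% / 5.0% |
| 25% | 2.8% / 3.7% | 8.8% / 12.8% |
| 0% | 1.8% / 2.2% | 28% / 40% |

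Each cell has 1,200 runs (standard error about 0.6 points near 5%). Repeat runs reached 8.2% on the birth clock and 41% on the randomisation clock.

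A second model used failures a mean of one month after birth and latency of 1.0 versus 0.5 month. Its two-sided error was about 5% from birth and 7 to 10% from randomisation. At 36% versus 65.7%, its power moved from 68% to 80% by clock alone.

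**The case against.** The strongest reply is that the log-rank test is named only to derive the sample size. Nothing says it will be the final analysis, and an SAP that is not shown may set another. This stands. A reader might infer from the heading Sample size and Statistic that the trial will be tested this way; the inference is reasonable but not stated, so every bias figure above is conditional. The mismatch does not depend on it. If the SAP tests the binary outcome, the 34 per group is unsupported; if it uses the log-rank test, the endpoint is no longer the one under Outcomes.

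Three further limits hold:
- The clock is not wholly open. The outcome is set one year after delivery and Table 1 counts follow-up in days postpartum, which favours a birth origin. Only the origin of the test, and of the one-year individual follow-up, is unstated.
- A reader might conclude that a birth clock penalises the flush arm. The document does not support that as a general claim. The effect needs a large share of failures dated at 36 weeks, and the article gives no such split; it mentions 36 weeks only for secondary outcomes.
- A reader might blame the whole power shortfall on the test or clock. The log-rank test with the stated one-year follow-up itself has only 65 to 71% power, so most of the gap comes from the follow-up assumption behind 34.

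**Conclusion.** The point holds as a mismatch between endpoint and sample-size method, and it should be corrected. From the article's own rates, the stated 80% is about 70% for the one-year binary comparison at the planning rates, 74% at the more optimistic 67%, and 65 to 69% after the planned loss. These figures need no assumption about event timing.

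The dependence on the clock is real but conditional. It matters only if the log-rank test is the primary analysis, and its size rests on assumed latency and event dating. From randomisation, the direction (favouring flush) held under every timing split tried, at about 5 to 41% one-sided. From birth, error against flush ranged from nominal to about 8%. The mismatch and the power figures carry high confidence; the individual error rates carry less.

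**What to change.** In Sample size and Statistic, and in the SAP, state that the primary analysis compares, in all randomised pregnancies, the proportion alive without major morbidity one year after delivery. Report it as a risk difference with 95% CI and a two-proportion test. Count fetal or neonatal death after randomisation as failure. Keep time-to-event curves as description, with their time origin stated. Restate the power of 34 per arm for that test. Rules for missing outcomes and any covariate adjustment can stay in the SAP.

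This needs wording and a recalculation, and no new data. It should be settled before any unblinded analysis, because the choice of test or clock could decide the result of a 68-patient trial. The cost is a less favourable power statement: about 70% before loss. Restoring 80% at 36% versus 65.7% would mean 2 × 49 = 98 women after 10% loss, against the planned 68.
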